**6. APPENDIX C: AMENDMENT HISTORY**

| Amendment No. | Protocol Version No. | Date issued | Author(s) of changes | Details of Changes made |
|----------------------|-----------------------------|--------------------|-----------------------------|--------------------------------|
|                      |                             |                    |                             |                                |

Protocol amendments will be submitted to the REC and recorded in the Amendment History form.

PREVENT-PTSD

**A randomised controlled trial to prevent PTSD, depression, and associated health problems in student paramedics (PREVENT-PTSD)**

### 777 Changes from previous version of SAP

778 A summary of key changes from earlier versions of SAP, with particular relevance to  
779 protocol changes that have an impact on the design, definition, sample size, data  
780 quality/collection and analysis of the outcomes will be provided. Include protocol version  
781 number and date.

| Version number
Issue date | Author of
this issue | Protocol Version & Issue
date | Significant changes from
previous version together with
reasons |
|------------------------------|-------------------------|----------------------------------|-----------------------------------------------------------------------|
| V1_ 21042021          |                         | Protocol_ Wildetal2018    | Not applicable as this is the 1 st
issue                |
|                              |                         |                                  |                                                                       |

782

783

## **BACKGROUND AND OBJECTIVES**

### **Background and rationale**

Emergency workers are at risk for major depression (MD) and posttraumatic stress disorder (PTSD), and an associated risk of poor physical health due to the nature of their work.[1] To date, interventions aimed at reducing risk of mental ill health in this population have been unsuccessful. Randomised controlled trials (RCT) found that trauma risk management, a peer support system widely available to the police and ambulance services in England, [2] critical incident stress debriefing widely used by UK fire-services, [3] and the charity Mind's six-session group-based resilience intervention had no effect on resilience or rates of mental ill health [4]. More effective preventative interventions for emergency workers are urgently needed.

Established interventions may have been unsuccessful because they fail to target predictors of mental ill health and are offered to emergency workers after rather than before repeated exposure to the stresses linked to their work. Moreover, cognitive strategies that could help them cope with characteristic stressors are not included as part of the training. For example, our and others' research has demonstrated that exposure to trauma or stressful scenarios through imagery reduces anxiety for police officers and other at risk populations. [5, 6] Development of more effective interventions requires identification of predictors of mental disorders and an understanding of how to modify them.

In a series of experimental and prospective studies, we identified two cognitive factors that are robust predictors of poor mental health in emergency workers: rumination (repetitive negative thinking) and resilience appraisals. Those who reported ruminative thoughts during critical incidents were more likely to experience poor levels of coping. [7] Adaptive appraisals during analogue trauma led to more successful attempts to regulate

emotions and fewer PTSD symptoms. [8] Our large-scale prospective study of newly recruited paramedics investigated predictors of PTSD and MD derived from cognitive theories of PTSD and depression. [1] Rumination at the start of paramedic training uniquely predicted PTSD; low resilience uniquely predicted an episode of MD.

We then developed an intervention to modify peri-traumatic ruminative thinking (i.e., thinking repetitively in an abstract way during trauma). Training to think in a concrete style (e.g., focusing on objective details and the sequence of events) led to significantly fewer intrusive memories and PTSD symptoms than individuals trained in a ruminative style. [9] We also applied one of the core techniques of a successful treatment for PTSD (cognitive therapy for PTSD,[10]), updating the memory of the stressful event with helpful information, as a preventative strategy for dealing with analogue trauma and found that it was more helpful in reducing repetitive thinking and PTSD symptoms than control interventions including exposure. [11]

Research has further demonstrated that exposure to trauma or stressful scenarios through imagery reduces anxiety for police officers and other at risk populations, and that internet-based cognitive treatment that includes attention training as a core component significantly reduces anxiety. [5, 6, 12]

## **Neurobiological Factors linked to PTSD and MD**

Genetic and longitudinal studies suggest that inflammation is a pre-existing vulnerability factor for the development of PTSD in trauma-exposed individuals rather than simply a correlate of subjective distress, disease severity, or maladaptive coping strategies following PTSD onset. [13, 14] For example, brain imaging studies have shown that high inflammation levels may increase threat perception (negative valence). Peripheral

administration of lipopolysaccharides (LPS), residues from bacterial cells' components known to elicit a strong systemic inflammatory response, potentiates amygdala activity in response to socially threatening stimuli (fear faces).[15] In turn, greater pre-treatment amygdala reactivity to threat predicts less symptom reduction during CBT.[16] Additionally, inflammation is an important risk factor for depression and cardiovascular disease, which frequently accompany PTSD.[17-19] Our study will investigate the link between inflammation and the development of PTSD and MD in trauma-exposed student paramedics.

We will investigate whether or not iCT-R can reduce levels of clinically-relevant inflammation levels, such as C-Reactive Protein (CRP), known to increase risk of psychiatric as well as cardiovascular and metabolic conditions comorbid with PTSD and MD. Given the wealth of literature supporting a relationship between the stress hormone, cortisol, and PTSD and MD, we will also systematically assess the cortisol awakening response (CAR) and diurnal cycle. The CAR is an endocrine marker, defined as the change in cortisol concentration that occurs during the first hour after waking from sleep.[20] A meta-analysis of 62 studies concluded that increases in the CAR were associated with job stress and life stress and linked to greater fatigue, burnout and exhaustion and risk for later health states, such as coronary heart disease.[21] A recent study found that higher CAR predicted future episodes of MD within a 2.5-year period.[20] We anticipate that iCT-R will reduce the CAR and cortisol throughout the day and protect against the development of PTSD and MD.

## **Objectives**

The primary trial objective is to evaluate whether the newly developed iCT-R intervention is more effective than the existing Mind-Online intervention at 1-year and at 2-years follow-up with regards to PTSD and MDD diagnoses.

Secondary trial objectives are to evaluate the efficacy of iCT-R compared to Mind-Online at 1-year and at 2-year follow-up with regards to secondary outcomes, such as resilience and well-being measures, as well as general health measures, and in terms of health economic costs. Furthermore, the effects of iCT-R versus Mind-Online on immune and hormone function will be compared at post-intervention.

Tertiary trial objectives are to investigate whether risk factors and predictors at baseline, such as level of social support, trauma exposure, demographic data, neuroticism as a personality factor, level of concrete thinking, frequency, duration, and distress with regards to intrusive memories influence any effects of iCT-R on PTSD and MDD diagnoses, psychological distress, and well-being at 1-year follow-up.

Further tertiary objectives are to investigate whether changes from baseline to post-intervention in resilience factors, such as rumination, responses to intrusive memories, level of concrete thinking, and resilience appraisals, predict PTSD and MDD diagnoses at 1-year follow-up in the iCT-R intervention group.

## **STUDY METHODS**

### **Trial Design/framework**

#### **Interventions:**

The study is a single-blind (assessors blind) randomised controlled trial. There are three arms: iCT-R, Mind-Online, and Standard Practice. The newly developed intervention iCT-R aims to modify rumination and appraisals linked to low resilience and risk for PTSD and MDD with a six-session supported online intervention. A trained research assistant provides email feedback on students' responses and, through an automated SMS programme, sends regular reminders of key points of the intervention and notifications to practice the skills. The other intervention also contains six online modules and includes information and advice about stress, sleep problems, anger, depression, PTSD, and mindfulness. Participants will receive the same frequency, type and duration of online support as in iCT-R. The third

arm is Standard Practice. Participants have access to the usual support offered through their university, but they will not receive any online modules or online support.

Time points:

Data are collected pre-intervention, post-intervention, at 6-months follow-up, at 1-year follow-up and at 2-years follow-up.

More information on the intervention arms and measurement time points can be found in the published trial protocol ([name] et al., 2018).

## **Randomisation and Blinding**

Participants are randomised on a 1:1:1 ratio as per a computer-generated randomisation schedule by OCTRU (Oxford Clinical Trials Research Unit) stratified by site, gender and baseline PHQ-9 score ( $\geq 9$  vs.  $< 9$ ) and PCL-5 score ( $\geq 33$  vs.  $< 33$ ). The researchers inform participants of the intervention they are to receive after participants have completed baseline assessments. Outcome assessment is single blind. Online questionnaires throughout the intervention and follow-up time points are completed without any involvement of the researchers. The clinical interview is done by an independent assessor, who is blind to treatment allocation. All personnel involved in the blood and saliva samples are blinded to intervention allocation. Due to the nature of the interventions, participants cannot be completely blinded to allocation.

## **Sample Size**

There are no interventions for emergency workers which target modifiable risk factors. Power calculation was approximated using the results of a study with a similar approach. Topper et al. (2017) found that an intervention targeting rumination reduced rates of depression in adolescents at 1-year follow-up by 57% compared to wait-list. We estimated that iCT-R, which also aims to reduce rumination, would reduce PTSD and MDD diagnoses by 50% in comparison to Mind-Online which has shown no change in rates of PTSD or MDD over time based on previous research. Setting power at 80%,  $\alpha = 0.05$  and hypothesising a reduction of relative risk of 50% results in an OR of 0.429 requires a total sample size of  $n = 304$  to show a risk reduction of 50% between iCT-R and Mind-Online. Therefore, each intervention arm requires  $n = 152$ . Including the third treatment arm, which is

Standard Practice, the total sample size required is  $n = 456$ . Allowing for 20% attrition, a total sample size of  $N = 570$  is required.

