### 11.2 The Number of Participants

We plan to recruit 570 participants.

The risk of student paramedics developing full syndromal PTSD and MD over two years without intervention is 10% (1), and 25% if subsyndromal PTSD and MD that cause significant distress are included. We predict that our intervention will reduce the relative risk by 50%. Setting power at 80%,  $\alpha=.05$  and hypothesizing a reduction of relative risk of 50% gives an odds ratio of 0.429, which requires a total sample size of N=304 to show a risk reduction of 50% between the active and placebo intervention. Thus, each condition would require N=152. Since we have a third condition (no-training control), the total sample size required would be N=456. Allowing for a 20% rate of attrition, we will require a total sample size of N=570.

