#### **Timing of Final Analysis**

Originally, as stated in the published trial protocol ([name] et al., 2018), we had planned to analyse the trial data once the trial was finished at two year follow-up. However, the outbreak of the Covid pandemic may have added additional risk to the mental health of emergency workers and therefore, if iCT-R leads to improvement in emergency workers' mental health compared to Mind-Online or Standard Treatment, it would be beneficial to roll out the intervention as soon as possible. It has been discussed and agreed with the Trial Steering Committee that data could be analysed early, namely after completion of the 1-year follow-up period, if rates of PTSD and MDD diagnoses in the total sample at 1-year follow-up are higher than expected. At 1 year follow-up, in the total sample, rates of PTSD are 8.7% compared to 8.3% in non-intervention studies of this population [1] and the general population rate of 3%. Rates of depression are 15.8% compared to 10.6% in non-intervention longitudinal studies of this population [1] and the general population rate of 10.3%. Since

there are higher than expected rates of PTSD and MDD diagnoses at 1-year follow-up in the total sample we now plan to analyse data at 1-year follow-up. Two-year follow-up data (including sub-thresholds) will be analysed by including them into the 1-year outcome models once they have been completed.

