#### **Description of Compliance with Intervention**

Level of compliance will be defined as 1) number of online modules completed during the intervention, 2) practice of tools.

A complier-average causal effect analysis (CACE) is used to test any influence of compliance on the intent-to-treat intervention effect of the primary trial objective analyses.

1067

1068

1069 **Reliability**

1070           The primary outcome measures, such as Structured Interviews by clinicians and self-  
1071 reports for the primary outcomes and nearly all of the secondary outcome measures are  
1072 standard instruments that have been validated and have shown good reliability.

1073           Scoring is done as described in the manuals or publications for the measures and  
1074 relevant sub-scales and Cronbach's Alphas are reported for the study sample.

1075           Interrater-reliability is reported for 1-year follow-up data. 10% of diagnoses at 1-year  
1076 follow-up are rated by a second rater.

1077           To ensure consistency in the data, validation checks on the data are carried out before  
1078 locking the dataset and analysis of the data. These include checking for potential data entry  
1079 mistakes, duplicate records, checking the range of variable values, missing data value codes,  
1080 etc.

1081 **ANALYSIS**

1082 **Outcome Definitions**

1083 Outcome measures:

1084           The primary outcome measure for the primary trial objective is PTSD and MDD  
1085 diagnoses (SCID-5;). Secondary outcomes with regards to the primary trial objective are  
1086 PTSD symptom severity (PCL-5) and MDD symptom severity (PHQ-9).

1087

1088           Outcome measures for the secondary trial objectives include resilience measures  
1089 (Wagnild-Resilience Scale and CD-RISC, both continuous), well-being measures (subscale  
1090 rumination of the RIQ, GAD-7, GHQ-12, WEMWBS), general health measures (weight and  
1091 height; Insomnia severity index; Smoking Behaviour Questionnaire, sum score for both  
1092 items; Alcohol Use Questionnaire, unit increase/ decrease/ stayed the same), health economic  
1093 costs (intervention costs per QALY gained based on 4 measures), and hormone and immune  
1094 function (collected with saliva samples and CRP plasma).

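### The SAP attaches 80% power to PTSD and MDD diagnoses, but its OR of 0.429 and 152 per arm fit only the 25% two-year outcome that includes subsyndromal cases; at the protocol's 10% full-syndromal rate, power is about 38%

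*Combined protocol and SAP*

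**What the plan says.** **Protocol 11.2** gives two control risks, in these words: "developing full syndromal PTSD and MD over two years without intervention is 10% (1), and 25% if subsyndromal PTSD and MD that cause significant distress"; that is, the 25% counts subsyndromal cases as well. It predicts a 50% relative reduction and arrives at OR 0.429, 304 for two arms, 152 per arm, 456 for three arms and 570 after 20% attrition. It does not say in words which of the two risks was used. The protocol's primary objective (Synopsis and section 5) counts subsyndromal PTSD and MD as cases.

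**SAP 3.3** carries over the same figures: "hypothesising a reduction of relative risk of 50% results in an OR of 0.429", then 304, 152, 456 and 570 at 80% power. It prints no control risk and does not mention subsyndromal cases. It states the effect as "We estimated that iCT-R, which also aims to reduce rumination, would reduce PTSD and MDD diagnoses by 50% in comparison to Mind-Online".

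**SAP 6.1** says "The primary outcome measure for the primary trial objective is PTSD and MDD" diagnoses, by SCID-5. SAP 2.2, 3.7 and 6.2 agree. None of them says whether this is one composite or two separate outcomes.

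**SAP 3.5** is the only place in the SAP where sub-threshold cases appear: "Two-year follow-up data (including sub-thresholds) will be analysed by including them into the 1-year outcome models once they have been completed". It also gives pooled 1-year rates of 8.7% for PTSD and 15.8% for depression, against reference rates of 8.3% and 10.6% from earlier non-intervention studies.

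**The concern.** The SAP prints a power figure beside an outcome for which it does not appear to have been derived. The protocol's two control risks differ by a factor of 2.5, and power for a 50% relative reduction depends heavily on the control risk. A sample size that suits 25% is far too small for 10%.

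The consequence is for interpretation. SAP 3.5 adds a 1-year analysis to inform early roll-out. If that analysis shows no difference in diagnoses, readers will take it as the result of a trial with 80% power to detect a halving, although the planning rates do not support that figure for full diagnoses.

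**Working it through.** **Inputs.** Two-sided alpha 0.05 (SAP 4.1), 80% power, 50% relative reduction, 1:1 between any two arms, 152 evaluable per arm (protocol 11.2 and SAP 3.3). Control risks 10% and 25% over two years (protocol 11.2).

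**Step 1: which control risk does OR 0.429 imply?** If control risk p is halved, OR = [0.5p/(1 − 0.5p)] / [p/(1 − p)] = (1 − p)/(2 − p).
- p = 0.25: 0.75/1.75 = 0.4286, the printed value.
- p = 0.10: 0.90/1.90 = 0.474.

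The SAP does not print 25%, but its odds ratio and its 50% reduction together fix it.

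**Step 2: reproduce the plan's sample size.** Pooled two-proportion formula without continuity correction:

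n per arm = [1.960·√(2p̄(1 − p̄)) + 0.842·√(p1(1 − p1) + p2(1 − p2))]² / (p1 − p2)²

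- 25% vs 12.5%: p̄ = 0.1875; n = (1.0819 + 0.4586)² / 0.125² = 151.9, so 152. Then 2 × 152 = 304, 3 × 152 = 456 and 456/0.8 = 570. Every printed figure is reproduced.
- 10% vs 5%: p̄ = 0.075; n = (0.7301 + 0.3121)² / 0.05² = 434.4, so 435. Three arms would need 1,305 evaluable, or 1,632 with 20% attrition.

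**Step 3: power at 152 per arm for 10% vs 5%.** z = (0.05·√152 − 0.7301)/0.3708 = (0.6164 − 0.7301)/0.3708 = −0.306, which gives 38.0%. Other uncorrected methods give 36.9% to 38.9%, and exact enumeration of the chi-square test gives 37.4%. With no attrition (190 per arm) it is 45.6%.

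**Step 4: other readings of the outcome.** Risk halved, 152 per arm. Overlap between the two diagnoses is not given, so composites run from full overlap (the larger single rate) to none (the sum).

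| Outcome and source of control rate | Control rate | Power |
|---|---|---|
| Full or subsyndromal, protocol 11.2 | 25% | 80% |
| Full syndromal, protocol 11.2 | 10% | 38% |
| PTSD, SAP 3.5 reference | 8.3% | 32% |
| MDD, SAP 3.5 reference | 10.6% | 40% |
| Either, SAP 3.5 reference | 10.6% to 18.9% | 40% to 66% |
| PTSD, pooled 1-year rate taken as control | 8.7% | 34% |
| MDD, pooled 1-year rate taken as control | 15.8% | 57% |
| Either, pooled 1-year rates taken as control | 15.8% to 24.5% | 57% to 79% |
| Either, pooled rates as a three-arm average with iCT-R halved | 19.0% to 29.4% | 66% to 87% |

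In the last row, pooled = (c + c + 0.5c)/3, so c = 1.2 × pooled. This assumes that Mind-Online and Standard Practice share one rate. A 25% composite there allows at most 29.4 − 25.0 = 4.4 percentage points of overlap, out of a possible 1.2 × 8.7 = 10.4.

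**The case against.** **No arithmetic is wrong.** That stands. All the printed figures are reproduced. The fault is that a correct calculation is attached to a different outcome.

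**The figure of 38% holds only near a 10% control rate.** This also stands. A reader might infer that the primary analysis has under 40% power and would more likely than not miss a true halving. The documents do not support that in general. The SAP leaves open whether the diagnoses form a composite, and a composite at the pooled 1-year rates could approach or exceed 80%. Those rates were learned during the trial, however. They are not the stated basis of the calculation, and the SAP specifies no such composite.

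**The power model is not the SAP's model.** The SAP specifies logistic mixed models with repeated assessments and baseline covariates, and group comparisons follow only after a significant global test. These features could raise or lower power, so the percentages are benchmarks. They are still the right ones for judging the printed figure, which comes from a two-proportion calculation, and the protocol's main analysis of rates is a chi-square test.

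**The 2-year outcome may include sub-thresholds.** SAP 3.7 makes 2 years the main time point, and the parenthesis in SAP 3.5 could mean that the outcome there matches the 25% in the protocol. A reader might go further and infer that the SAP will certainly mix two case definitions in one repeated binary outcome. That is one reading of a parenthesis; the text is ambiguous. It does not rescue SAP 3.3, which speaks of diagnoses without qualification.

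**The sample size could no longer be changed by April 2021, and intervals will be reported.** True, but the power statement still frames how a null result is read.

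**Conclusion.** The point holds as an inconsistency between the power statement and the outcome. OR 0.429, 152 per arm and 80% power belong to 25% against 12.5%, which the protocol gives as a two-year risk including subsyndromal cases. SAP 3.3 presents them as power for diagnoses.

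At the protocol's 10% full-syndromal rate the same numbers give about 38%. At the SAP's reference rates power is 32% for PTSD, 40% for MDD, and at most 66% for a composite. The composite figures rest on assumed overlap, and all figures assume a halved risk in a single two-arm comparison. Neither protocol risk is a 1-year figure, so nothing in the documents supports 80% power for the 1-year analysis as planned.

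**What to change.** **1. Restate SAP 3.3.** Say that:
- 152 per arm gives 80% power for full or subsyndromal PTSD or MD over two years, at 25% against 12.5%;
- for full syndromal cases over two years at 10% against 5%, power is about 38%;
- no 80% claim is made for the 1-year analysis of diagnoses.

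Print the control risks and say that the figures refer to a two-proportion comparison. This costs wording only and changes no test or estimate; the stated power for diagnoses becomes less favourable.

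**2. Reconcile the primary outcome.** SAP 3.7 and 6.1 name diagnoses, SAP 3.5 adds sub-thresholds at 2 years, and the protocol's objective includes subsyndromal cases. The SAP should state whether the primary outcome is one composite or two outcomes, and use one case definition at 1 and 2 years within any single model. If subsyndromal cases are included, it needs an operational definition; protocol 11.2 offers only significant distress. This is a decision on the endpoint and more than a wording change, because pooled 1-year rates were already known when the SAP was written. The choice and its reasons should be documented before any comparison by arm. No extra participants are needed.
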